## Are any of the following an exclusion criterion?

---

26.

*Check all that apply:*

- ✓ Age
- ✓ Gender
- Race or Ethnicity

Language

Not applicable

\*required

**Provide a justification for how this exclusion does not adversely affect the rights and welfare of participants:**

---

27.

Those individuals less than 18 and greater than 35 years of age will be excluded. Participants younger than 18 are excluded due to necessity of parental consent. Participants greater than 35 years old are excluded for two reasons. First, the primary demographic of our society which resistance trains and will consider using various dietary supplements to augment their training adaptations fall within this range. Second, as males reach 35 years of age, circulating levels of androgens begin to decrease which is associated with declines in strength, power, and muscle size. Additionally, known influences of female sex steroid hormones impact how strength and body composition adaptations occur. Due to this study being an initial pilot, females are excluded to avoid the confounding influence of changes in female sex steroid hormones across the menstrual cycle.

\*required

**Will you be enrolling any of the following populations?**

28.

*Check all that apply:*

Minors

Pregnant Women or Fetuses

Prisoners

☒ Not applicable

\*required

**Are you enrolling any vulnerable populations?**

29.

*Check all that apply:*

Individuals with Impaired Decision-Making

Economically Disadvantaged

Educationally Disadvantaged

☒ Not applicable

\*required

31. **Are you enrolling participants with special cultural considerations or who reside in a different country?**

---

☒ No

Yes

\*required

32. **Is anyone on the research team in a position of authority over participants?**

---

*This type of relationship could include, but is not limited to, the following:  
supervisor/staff, teacher/student, coach/team members, counselor/client.*

No

☒ Yes

\*required

**How will the recruitment process ensure participants do not feel coerced into participation?**

---

*Coercion occurs when someone feels overtly or implicitly obligated to participate based on some aspect of their relationship with the researcher.*

It is anticipated that study participants will be recruited from within and outside the Lindenwood University community. However, faculty members at Lindenwood

32a.

University may have students in his/her classes that are participants in this study in which a research requirement will be required as part of the requirements for their class. In these situations, all students have four options to receive credit for this assignment: a) observe data collection, b) participate in a study, c) attend a scientific conference, or d) attend a thesis proposal or defense. Thus, any study participant who is also a student in a faculty member's class will have the same opportunities to complete this requirement as all other students. If the study participant elects to not participate in this study, they have other means to earn credit for this class requirement. This requirement is clearly outlined in each of the relevant course syllabi.

\*required

**How are you recruiting participants?**

33.

*Check all that apply:*

Lindenwood Participant Pool

Participant Registry or Database

✓ Flyer

Telephone Script

✓ Email Script

✓ Social Media Script

Website

✓ Classroom Presentation

✓ Other Recruitment Method(s)

**33b. Flyer Recruitment**

\*required

Where will you post flyers?

33b-1. *If posting flyers at Lindenwood University, please indicate the specific buildings in which flyers will be posted.*

Lindenwood University and public places within the St. Charles area (such as grocery stores and gymnasiums). Lindenwood buildings may include the Field House, Spellman Center, Evans Commons, and the Library.

\*required

Does posting flyers require approval?

- 33b-2. *Other sites may or may not require permission. You are required to ensure compliance with the requirements at each site.*

*Note:* All posting of flyers on Lindenwood University sites requires prior permission. Approval from the Dean or building coordinator for each area must provide approval for the posting of research recruitment materials in their area.

✓ No

Yes

\*required

Attach all flyers you will use for recruitment.

33b-4.

[Dileucine Training Study Flyer.pdf](#)

\*required

33d. **Email Script**

\*required

How will you obtain email addresses?

33d-1.

Through initial contact initiated by study participant. Participants may call or email the lab and express interest.

\*required

**Does your email recruitment process require prior authorization or approval?**

33d-2.

Note: Lindenwood University will not release student email addresses for research purposes. If you plan to recruit subjects on the LU campus via email, please contact the Dean or supervisor most closely related to those subjects for permission for them to distribute your recruitment email at their discretion.

✓ No

Yes

- 33d-3. Attach a record of authorization for use of emails for research recruitment purposes (such as an email or formal approval).

Attach the script you will use to recruit participants through an email.

33d-4.

---

[DTS EMAIL SCRIPT.docx](#)

\*required

33e. **Social Media Script**

---

\*required

Where will you post information, and how do Terms of Service apply to this posting?

---

33e-1. *Researchers are required to be aware of the Terms of Service and expectations for posting in social media or online spaces. As these Terms of Service may change over time, researchers may need to modify this section of the application as these terms or expectations change.*

Information about the study will be posted on the EPNL's Instagram, Twitter, and Facebook page.

Attach the script you will use to recruit participants over social media.

33e-2.

---

[SOCIAL MEDIA SCRIPT-2021.01.22.docx](#)

\*required

32g. **Classroom Presentation**

---

\*required

Where and when will this take place?

33g-1.

---

This will take place at Lindenwood University. It will take place during classes when permission is given by the professor.

\*required

33g-2. Does this presentation require approval?

---

✓ No

Yes

\*required

33h. **Other Recruitment Method(s)**

---

\*required

33h-1. Describe your recruitment method:

---

Through Lindenwood's online platform InvolveU

Attach any relevant script or approval for this recruitment method.

---

33h-2. [SOCIAL MEDIA SCRIPT.docx](#)

[Dileucine Training Study Flyer.pdf](#)

\*required

**Does your research involve any of the following?**

34.

*Please contact the [IRB Office](#) if you have questions about making this decision. We are happy to assist in helping you select your review pathway.*

*Sensitive and Identifiable Information*

- ✓
- Your research is collecting data which fall under the LU IRB definition of Sensitive Data. You will also be collecting and retaining Identifiable Data.

*Physical, Pharmacological, or Psychological Intervention*

- You will be performing physical procedures such as, but not limited to, drawing blood or collecting tissue, having participants ingest nutritional supplements or performing an exercise bout or exercise training program.

✓

OR

- You will be performing behavioral procedures that may affect the behavior, mood, or ability of participants. These procedures are *not* brief in duration, harmless, or painless; they are potentially physically invasive; they may potentially have a significant adverse lasting impact on the subjects; or they may be offensive or embarrassing to participants.

*Vulnerable Populations*

- Some or all of your participants are likely to be vulnerable to coercion or undue influence, such as children, prisoners, individuals with impaired decision-making capacity, or economically or educationally disadvantaged persons.

*None of the above*

- If your study involves minors, you may select this option only if your research is conducted in established or commonly accepted educational settings, involving normal education practices.

## Consenting Adult Participants

---

\*required

### **How will you obtain informed consent from adult participants?**

---

*If multiple populations are consented, describe the different process and consent form used for each population when applicable. In thinking through your consent process, please describe:*

- 35.
- *Where you will consent participants, which should be a private area accessible to researchers and participants.*
  - *When you will consent participants, which should include time for participants to consider the research, ask questions, and consult with family, friends or physicians. The timing of the consent process should not cause undue inconvenience or hardship to participants.*
  - *How the consent process will take place, including any issues you anticipate in terms of the vulnerability or accessibility of potential participants.*

Most commonly, participants will be consented inside the Exercise and Performance Nutrition Laboratory. When possible, interested participants will be provided a consent form via email to give them more time to review and formulate questions. All participants will be given as much time as necessary to formulate questions and consult family, friends, physicians, and whomever else they would like. Prior to any data collection and at a time they schedule, potential study participants will, after having their questions answered, sign and date the consent form.

\*required

### **Are you requesting a Waiver of Documentation of Consent?**

---

*A Waiver of Documentation of Consent is used when:*

- 36.
- *You are providing an Informed Consent Document to participants, but will not be obtaining their written signatures.*

- *Reading an Informed Consent script verbally, or over the phone, to participants when conducting a screening conversation and sharing study requirements.*

No

✓ Yes

\*required

*Select one of the following and then provide a rationale explaining why this Waiver of Documentation of Consent will not adversely affect the rights and welfare of participants:*

36a.

---

The only record linking the subject and the research would be the consent document, and the principal risk would be potential harm resulting from a  
 ✓ breach of confidentiality. Each subject will be asked whether the subject wants documentation linking the subject with the research, and the subject's wishes will govern.

\*required

How will the rights and welfare of participants be protected, even though you will not be obtaining documentation of informed consent from participants?

---

36a-1.

After the phone or email screen, any and all gathered information will be kept in a secure and locked filing cabinet behind two locked doors. Once participants arrived to the EPNL, any further questions the participant may have will be answered and full consent will take place at that time. No harm should come from asking participants to complete an overnight (8 - 10 hour) fast. Most people from the time of their last meal (dinner) until the time of their first meal (breakfast) the next day will have gone through the same overnight fast, if not longer. Furthermore, several studies have shown that ~20 - 30% of adults will all-together skip breakfast (St. Onge et al. 2017; Greenwood 2007; Sungsoo et al. 2003; Ruxton 1997; Haines 1996) [References attached]

The research presents no more than minimal risk of harm to subjects, and involves no procedures, for which written consent is normally required outside of the research context.

\*required

**Are you requesting a Waiver of Consent or will you be altering or removing any of the required Elements of Consent?**

37.

*A Waiver of Consent is used when you will not be obtaining any informed consent from participants. This is rare occasion, typically used when a signature would normally be required, but contacting each potential participant would be impracticable.*

☒ No

☐ Yes

**Attach all of your Adult Informed Consent Documents:**

38.

*All current Lindenwood University Research Informed Consent Documents and Information Sheets are [available here](#). These templates include instructions. Sections indicated in these templates may not be revised or altered by researchers.*

[DTS - Consent Form.12.3.20 \(2\).docx](#)

[DTS - Consent Form.01.20.21.docx](#)

### **Consenting Minor Participants**

\*required

**Are you enrolling minor participants?**

39.

*A minor is defined as a participant under the age of 18 at the time of enrollment. If research is being conducted in an educational environment, please visit our [guidance for K-12 research](#).*

☒ No

☐ Yes

### **Other Participant Considerations**

---

\*required

40. **Are you enrolling Prisoners?**

---

☒ No

☐ Yes

\*required

41. **Are you enrolling Pregnant Women, Neonates, or Fetuses?**

---

☒ No

☐ Yes

\*required

42. **Are you enrolling any participants who by virtue of a cognitive, health, social or other reason may not be able to provide informed consent?**

---

☒ No

☐ Yes

\*required

43. **Are you enrolling participants who do not speak English, or who may not have English proficiency?**

---

☒ No

☐ Yes

\*required

### Are you collecting Personally Identifiable Information?

---

According to [Lindenwood University IRB policy](#), this could include:

- 44.
- Any data element which singly or in combination could be used to directly identify a participant. The LU IRB uses the list HIPAA identifiers as a helpful guide.
  - Any combination of variables in a data set that might permit the indirect identification of a participant.
  - Any element of the research design, such as timing or location, that may permit the incidental identification of participants.
  - Any code linking a participant and their data.

No

✓ Yes

\*required

44a. Check all that apply:

---

- ✓ Location information (address, geotagged data, etc...)
- ✓ Dates related to an individual (birth date, graduation date, dates of service, etc...)
- ✓ Phone numbers
- ✓ Email addresses
- ✓ Social Security Numbers
- IP Addresses
- Biometric Identifiers (finger or voice print, unique biomarkers, etc...)
- Photographs, video, or audio
- Other:

\*required

### How will you maintain participant privacy and confidentiality?

---

*Describe all protective measures taken while collecting, recording, handling, and storing research data. Provide details on any methods used to deidentify, code, or transfer data.*

45. Only information required to accurately complete all aspects of testing in this study will be collected. Participants will be kept anonymous during data collection, storage, and release by all research team members following standard confidentiality protocols. All data will be de-identified by assigning each participant a unique, random identification number. Hard copy data will be kept in a locked filing cabinet inside of the Exercise and Performance Nutrition Laboratory, which is locked when not occupied by staff/student workers. All electronic data is password protected. All electronic data will be kept on a password protected computer for no longer than 3 years. All data from participants who do not qualify will be destroyed. All biological samples transferred elsewhere for analysis will only be labeled with the participant's unique, random identification number.

\*required

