### Baseline Testing (Visit 2)

At least three days after Visit 1 to allow for completion of their food record, participants will return to the lab to complete their first testing session and begin following the resistance training and supplementation regimens. Participants will first have their body mass assessed before providing a urine sample and completing their body water, DEXA assessments (i.e. 4-compartment assessment), and muscle thickness via ultrasound. This scan will be done between the hours of 0600-1000 following an overnight fast and hydration levels will be standardized through the use of urine specific gravity measurements using a hand-held refractometer. Participants will be sent a hydration protocol to follow 24 hours prior to their visit to help ensure adequate hydration levels. This protocol will instruct the participants how much water they should be consuming throughout the day. Prior to testing, participants will complete the same standardized warm-up consisting of 5 minutes of light cycling, 10 body weight squats, 10 body weight walking lunges, 10 dynamic walking hamstring stretches (straight-leg march), and 10 dynamic walking quadriceps stretches. After the warm-up,

participants will complete five CMJ with their hands on their hips. One minute of rest will be observed between each CMJ. Participants will have their maximal voluntary isometric contraction (MVC) completed using an isometric mid-thigh pull. Three attempts will be made and one minute of rest will be observed between each test. Participants will then have their 1RM determined using the leg press exercise. Three minutes of rest will be provided after 1RM is determined and each participant will perform repetitions to failure using 80% of their previously determined 1RM to determine their repetitions to fatigue (RTF). An additional 3-minute break will be observed and then bench press 1RM and RTF will be completed using identical procedures as the leg press exercise. After observing a three-minute rest period after completion of the bench press RTF participants will complete a Wingate using a load that is equivalent to 7.5% of their body mass to measure anaerobic capacity (Lode Excalibur Sport, Lode, Netherlands). Participants will then complete an education session with a research team member to outline the dietary goals they are required to meet throughout this study. This study visit will take approximately 90 minutes to complete.

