## Procedures

### Body Mass

Body mass weight will be measured (Tanita BWB-627A, Tokyo, Japan) and recorded to the nearest  $\pm 0.1$  kg upon arrival at all study visits. The recorded body mass during visit 1 and visit 2 will be compared to ensure the participant is weight stable and any participant whose body mass changes by more than 3% during this time will be excluded from participation. In addition, body weight will be assessed to compare changes seen after completion of the supplementation and resistance training protocols.

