### ***Adverse Event Reporting***

The occurrence of adverse events will be recorded throughout the entire duration of the study. When participants visit the laboratory during their weekly supervised workout, participants will report the frequency as well as the severity ('mild', 'moderate', 'severe') of any adverse event they report. In addition, adverse events will be collected through spontaneous reporting by the study participants, interaction of a research team member with a study participant, or through review of a study participant's compliance paperwork.

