## What disqualifies a participant for your research?

---

*Please include all exclusion criteria.*

25.

- Female
- Participants who are determined to not be weight stable defined as week 0 and week 2 body mass levels deviating by 3% or more.
- Any individual who is currently being treated for or diagnosed with a cardiac, respiratory, circulatory, musculoskeletal, metabolic, immune, autoimmune, psychiatric, hematological, neurological or endocrinological disorder or disease.
- Body mass index  $> 25 \text{ kg/m}^2$ . Individuals with a body mass index greater than  $25 \text{ kg/m}^2$ , but a body fat percentage less than 25% fat will be accepted into the study
- Individuals who present with any previous injury or illness that would prevent them from appropriately completing all exercise lifts.
- Participants who are not able to fit onto the DEXA table will not be able to participate in the research due to size restrictions of the equipment. This typically includes individuals exceeding 400 pounds or those greater than 6'4".
- Those individuals with less than 12 months of structured resistance training experience will be excluded from the study.
- Individuals whose maximal relative upper body strength is below 1.0 will be excluded.
- Individuals whose maximal relative lower body strength is below 1.5 will be excluded.
- All participants who DO NOT abstain from taking any additional forms of nutritional supplementation deemed to be ergogenic or that will impact resistance training adaptations (pre-workouts, creatine, beta-alanine, etc.) for four weeks prior to beginning this study and for the entire duration of the study.
- Individuals who are currently using or have used within the past 12 months anabolic-androgenic steroids.

\*required

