**What will you do with data or specimens at the conclusion of the study?**

47.

---

*Check all that apply:*

I am not collecting any identifiers. I will retain data for the required retention period (3 years, or longer as required by other agencies) and then destroy it.

I will deidentify data or specimen logs and erase or destroy any related codes. I will retain data for the required retention period (3 years, or longer as required by other agencies) and then destroy it.

☒ I will keep identifiable data for the required retention period (3 years, or longer as required by other agencies) and then destroy it.

I will destroy any leftover specimens.

I will retain data and specimens for future use.

Other:

\*required

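### The rule to destroy data of participants who do not qualify is not limited to people screened out before randomisation, so it could be applied to randomised, dosed men

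*Protocol*

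**What the plan says.** In the answer on privacy and confidentiality (question 45): "All data from participants who do not qualify will be destroyed". The same answer caps storage of electronic data at three years.

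The exclusion criteria stand under the heading "What disqualifies a participant for your research" (question 25). Two of them matter here:

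- Weight stability: "Participants who are determined to not be weight stable defined as week 0 and week 2 body mass levels deviating by 3% or more".
- Abstention from other ergogenic supplements, required "for four weeks prior to beginning this study and for the entire duration of the study".

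At Visit 2 (week 0), participants are tested and "begin following the resistance training and supplementation regimens" (Baseline Testing). On weight stability, the Body Mass section differs from question 25: "The recorded body mass during visit 1 and visit 2 will be compared to ensure the participant is weight stable".

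On records, the Adverse Event Reporting section says: "The occurrence of adverse events will be recorded throughout the entire duration of the study". Question 47, on data at the end of the study, has this box ticked: "I will keep identifiable data for the required retention period (3 years, or longer as required by other agencies) and then destroy it".

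**The concern.** The application's own vocabulary links the destruction rule to the exclusion list: questions 24 and 25 are headed by what qualifies and what disqualifies a participant. If a man can become disqualified after he has been allocated and dosed, the rule as written covers everything collected on him up to then: body composition, strength and adverse events.

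Most weaknesses in an analysis plan can be repaired while the data exist. Destruction cannot. A later decision to analyse all randomised men could not bring the records back. Body-mass change and use of other ergogenic products are on-study events that may relate to assignment or response, so the lost men need not be a random subset. The Experimental Design section also plans to record and assess adverse events for each supplementation group, which cannot be done completely if some dosed men's logs are gone. Question 51 states that there will be no data and safety monitoring plan, so no such plan offers a second safeguard.

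**Working it through.** The point rests on wording and timing. The protocol gives no figure to reproduce beyond the sample size: 3 arms × 12 = 36, which agrees across the list of groups, question 22 and question 23.

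**Step 1: what the rule covers.** Question 45 refers to all data and to participants. It names no time point and makes no exception.

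**Step 2: when each criterion can be judged.**

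| Criterion | Where stated | When judged | Relative to first dose (Visit 2, week 0) |
|---|---|---|---|
| Supplement abstention | Question 25 | Four weeks before entry to study end | Partly after |
| Weight stability | Question 25 | Week 0 versus week 2 | After |
| Weight stability | Familiarization and Entry; Body Mass | Visit 1 versus Visit 2 | Before |
| Weight stability | Supplementation Protocol | Already established when men are assigned | Before |

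The abstention criterion extends past randomisation wherever randomisation is placed. The weight criterion does so under question 25 combined with the Visit 2 start of supplementation, but not under the other three sections.

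**Step 3: when randomisation happens.** The Baseline Testing text matches men on Visit 2 fat-free mass, so allocation cannot precede Visit 2. Table 1 marks randomisation in the Visit 1 column. On that row even the Visit 1 to Visit 2 weight check would follow allocation, though it would precede dosing. A rule phrased as before randomisation therefore needs one stated time for randomisation.

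**Step 4: the retention statements.** Question 45 gives three years as a ceiling for electronic data. Question 47 gives three years or longer. Keeping data for exactly three years meets both. They part only if another agency requires longer.

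**Step 5: scale.** One man is 1/12 = 8.3% of an arm. The protocol gives no rate of late disqualification. For an assumed rate q per man, independent across 36 men, the expected number is 36q and the chance of at least one is 1 − (1 − q)^36:

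| Assumed q | Expected men | Chance of at least one |
|---|---|---|
| 2% | 0.7 | 52% |
| 5% | 1.8 | 84% |
| 10% | 3.6 | 98% |

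The precision cost alone is modest. For one pairwise comparison (two-sided 0.05, 80% power, normal approximation), the detectable standardised difference is (1.960 + 0.842) × √(2/n). That is 1.14 at n = 12 per arm, 1.20 at 11 and 1.25 at 10. The weight of the point lies in possible non-random, irreversible loss, more than in lost power.

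**The case against.** A reader might infer that the protocol plans to destroy the data of randomised men, and that two exclusion criteria are settled as post-randomisation checks. The documents support neither inference.

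- In a privacy answer, not qualifying most naturally means failing screening. Question 36 confirms that information is gathered at a phone or email screen. Men lost later are described in other terms: the Dietary Protocol speaks of removal, and the compensation answer of not completing the protocol.
- The weight check is placed before assignment in Familiarization and Entry, Body Mass and Supplementation Protocol. The week 0 to week 2 wording might also reflect a run-in: the aims speak of eight weeks of supplementation, and the analysis takes Week 10 minus Week 2. On that reading the check again precedes allocation. Against it, Experimental Design gives ten weeks of supplementation and Baseline Testing starts it at Visit 2.
- No section describes how a supplement breach would be detected mid-study, or says that a breach undoes a man's qualification retrospectively.
- The adverse event section governs recording, not retention, so it does not by itself contradict question 45. Question 47's general commitment to keep data favours the narrow reading.
- The consent forms and adverse event log are attachments that are not shown and may settle the matter.

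Most of this stands. It turns a planned loss into a possible one and makes the weight criterion a contradiction to reconcile. It does not remove the gap: the abstention criterion is on the disqualifying list, it runs to the end of the study, and question 45 has no limit. The Dietary Protocol's removal rule is a withdrawal rule and plays no part in the argument.

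**Conclusion.** The point holds as a gap in wording with an irreversible consequence if the text is followed literally. Question 45 could be applied to randomised, dosed men through the abstention criterion on any reading, and through the weight criterion under question 25's wording only. Such use would sit badly with the retention commitment in question 47 and with the plan to assess adverse events by group. Whether any man would be affected is unknown, and the rates in the table above are assumptions. The mismatch between the three-year ceiling and the three-years-or-longer commitment is a minor matter of consistency. The case for changing the text is that an unrecoverable and possibly selective loss can be ruled out at almost no cost.

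**What to change.** 1. In question 45, replace the destruction sentence with wording such as: *Data from people screened out before randomisation will be destroyed, except for a de-identified count and the reason. All data from any randomised participant, including adverse event records, will be kept for the period given in question 47, whatever his later eligibility or withdrawal.*
2. Align the three-year cap on electronic data in question 45 with question 47.
3. Reconcile Familiarization and Entry, Body Mass, Supplementation Protocol and question 25 on when weight stability is judged, and Table 1 with the Baseline Testing text on when randomisation occurs, so that the cut-off in item 1 has one meaning. Which timing applies is for the investigators to decide.

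The cost is a few sentences in the application and, if the consent form describes data handling, a matching line there. No procedures, visits or participants are added.
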